### Analysis of secondary outcomes

For continuous variables, the mean and 95% confidence interval will be calculated for each group and t-tests will be used for group comparisons. For discrete variables, the number, proportion, and 95% confidence interval for the proportion will be calculated for each group, and the chi-square test will be used for group comparisons.

Regarding the breastfeeding proportion, ≥ 80% breastfeeding (daily milk amount ≤ 125 ml at 1 month postpartum and ≤ 164 ml at 6 months postpartum) will be used for between-group comparisons. Regarding the dietary items, the means and 95% confidence intervals will be calculated for each item at each time point (at the start of the study and 6 and 12 months postpartum) in the intervention group. The same analysis will be performed to analyze changes from the start of the study to 6 and 12 months postpartum.

For device usage, the use of activity tracker meters, wearing the weight/body composition monitor, and performance of measurements with the weight/body composition monitor at each time point (6 and 12 months postpartum) will be summarized and compared between the groups. In the group that will not use the devices at the beginning of the study, the number, proportion, and 95% confidence interval for the proportion will be calculated for participants who started using the devices at 6 and 12 months postpartum.

Regarding mobile application use, the mean and 95% confidence intervals will be calculated for the number of logins and viewing time at each time point in the intervention group (at 6 and 12 months postpartum). For uploading of meal images (at 6 and 12 months postpartum) and viewing of breastfeeding videos (during pregnancy and at 6 weeks postpartum), the number, proportion, and 95% confidence interval will be calculated for the intervention group.

Regarding the continuation of the intervention program (at 6 and 12 months postpartum), the number, proportion, and 95% confidence interval will be calculated for the intervention group.

Regarding adherence, the number, proportion, and 95% confidence interval for participants who enter data via the IoT devices and mobile applications ≥ 80% of the time during 2 weeks at each time point (at the beginning of the study and 6 and 12 months postpartum) will be calculated for the intervention group (using data from a data integration platform). In addition, the number, proportion, and 95% confidence interval of participants who will open the application and enter meals into the application for ≥ 4 days per week will be calculated for the intervention group.

### Subgroup analysis

The following subgroup analyses will be performed on the primary and secondary endpoints (pregnancy outcomes, body weight, body fat, blood pressure, impaired glucose tolerance, EPDS, diet, health, and breastfeeding):• Among those who will perform ≥ 80% or < 80% of measurements of body weight, body composition, and activity throughout the study period• Among those who will perform ≥ 80% or < 80% of measurements of body weight and body composition throughout the study period• Among those who will use the activity tracker for ≥ 80% or < 80% of the study period• Among those who will perform ≥ 60% or < 60% of measurements of body weight, body composition, and activity throughout the study period• Among those who will perform ≥ 60% or < 60% of measurements of body weight and body composition throughout the study period• Among those who will use the activity tracker for ≥ 60% or < 60% of the study period• Among those with body weight at registration ≥ / < the median• Among those with body composition measurement at registration ≥ / < the median• Among those with activity tracker measurement at registration ≥ / < the median

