### Intervention

The intervention will be initiated on the day consent is provided during pregnancy to 1 year postpartum. The IoT intervention for this trial is defined as (1) automatically generated advice based on data (weight, body composition, activity, sleep) measured using IoT devices and meal records and photographs recorded with a mobile application (Calo Mama Plus Pregnant woman Course®) and (2) provision of articles and videos related to obesity and pregnancy via a mobile application.

The following IoT devices will be distributed to all participants: body composition monitor and scale (HBF-227t, Omron Healthcare Inc., Tokyo) and fitness tracker (Fitbit Inspire®, Fitbit Inc., San Francisco, CA).

Participants in the intervention group will use a mobile application (Calo Mama Ninsanpu Plus®). The target weight 1 year postpartum has been set at 93% of the pre-pregnancy weight. Participants will monitor themselves daily to the extent possible using the IoT devices (weight and body composition monitor, activity, and sleep tracker) and by entering meal records and photographs into the mobile application.

The mobile application (Calo Mama Plus Ninsanpu Course®) has the following four functions: 

It automatically generates personalized advice based on conditions during and after pregnancy. Personalized advice is generated automatically based on data (weight, body composition, activity, and sleep) measured with the IoT devices and meal records and photographs recorded by the mobile application, alongside considering how far long in the pregnancy the participant is or the number of weeks postpartum.It provides articles based on the number of weeks of pregnancy or postpartum. The articles are delivered once or twice a week on themes that match the number of weeks of pregnancy or postpartum.It provides breastfeeding advice. After delivery, advice on breastfeeding is provided that reflects the breastfeeding status (number of times the participant recorded breastfeeding and amount of milk).It plots the body weight during pregnancy. Weight measurements during pregnancy are plotted on a graph and advice on weight changes based on the pre-pregnancy BMI is provided.

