### Data collection

All study participants must weigh themselves once at the start of the study and at 1, 6, 12, and 24 months postpartum and track their activity and sleep patterns for 1 week at the beginning of the study and at 6, 12, and 24 months postpartum. Body weight will be measured once a day in the morning using the weight and body composition monitor. Activity and sleep will be measured using an activity and sleep tracker, which will be worn on the non-dominant arm at all times, even during sleep, except during recharging (once every 5 days).

All participants will complete online questionnaires at the beginning of the study and at 1, 6, and 12 months postpartum. If any data are lacking, they will be collected from the medical records. Details of the questionnaires developed for this study are as follows (supplementary file):

Background and lifestyle (at the start of the study): items related to pregnancy and delivery history, medical history, family history, and exercise and dietary habits.Edinburgh Postnatal Depression Score (EPDS) (start of study, 1 month postpartum) [22].Breastfeeding status (intensity, duration) questionnaire (1, 6, 12 months postpartum).Breastfeeding process questionnaire (1 month postpartum).Behavioral changes (attitude, knowledge) (6, 12 months postpartum).User-friendliness of devices, barriers to lifestyle improvements and behavioral changes, areas for improvement, etc. (6, 12 months postpartum) (both groups).Desire to continue using the IoT devices after the trial ends (12 months postpartum) (intervention group only).

All participants will have blood samples taken at home via postal self-checkups at 6, 12, and 24 months postpartum to measure HbA1c, fasting glucose, total protein, albumin, AST, ALT, γ-GTP, total cholesterol, HDL cholesterol, triglycerides, urea nitrogen, creatinine, and uric acid. To collect blood samples, the trial secretariat will send test kits to the participants for postal self-checkups. Results of the postal self-checkups will be returned by mail to the participants within 6 weeks.

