### Sample size

Assuming a -2% weight change at 12 months postpartum compared to before pregnancy in the non-intervention group, the trial was designed to detect whether the IoT/mobile application intervention would result in a -5% weight change at 12 months postpartum. To conduct a two-sided test with a standard deviation of 8% and significance level of 5% at 80% power, 226 participants in both groups are needed. Assuming loss of approximately 20% of participants from exclusion or drop-out, the target number of registrations is set to 270 women.

There are 6,000 deliveries each year at the trial institutions. If 10% of the women are obese, the total number comes to 600 per year. As pregnant women at up to 30 weeks of gestation are eligible for registration, 250 pregnant women at up to 30 weeks of gestation who have already visited the outpatient maternity clinic for checkups and 250 pregnant women who newly visit during the 5-month registration period will be eligible. Hence, it is expected to be possible to register the target number of participants.

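### Six of the nine subgroups are defined by adherence after randomisation, so arms compared within them are not protected by randomisation and can differ spuriously in either direction

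*Protocol article*

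**What the plan says.** The Subgroup analysis section of the protocol article lists nine splits, to be applied to the primary endpoint and to most secondary endpoints, including pregnancy outcomes, the EPDS, diet and breastfeeding.

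- Six use adherence over the study period. There are three definitions (weight, body composition and activity measurements together; weight and body composition measurements; tracker use), each cut at 80% and at 60%. The first reads "Among those who will perform ≥ 80% or < 80% of measurements of body weight, body composition, and activity throughout the study period".
- Three are median splits of values at registration.

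The arms are asked for different amounts of measurement. In the Intervention section, for the intervention arm: "Participants will monitor themselves daily to the extent possible using the IoT devices". The same section requires the non-intervention arm to use the devices only at the data-collection points. The Data collection section sets a common minimum: "All study participants must weigh themselves once at the start of the study and at 1, 6, 12, and 24 months postpartum", plus one week of activity and sleep tracking at the start and at 6, 12 and 24 months.

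The Subgroup analysis section does not define the denominator for the share of measurements, does not restrict these splits to one arm, and does not label them exploratory or non-causal.

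**The concern.** Adherence over the study period is known only after randomisation, and it is behaviour that the intervention sets out to change. Women who reach a cut-off in one arm need not resemble those who reach it in the other. A difference between arms within a stratum then mixes any treatment effect with a difference in who was selected.

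Timing makes this worse. Pregnancy outcomes are fixed at delivery and the EPDS is last taken at 1 month, yet both would be stratified by behaviour that mostly comes later. Part of the adherence measure also falls after the 12-month primary endpoint. Women with few measurements are in addition the likeliest to lack the device-recorded 12-month weight.

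At stake is a table of results by adherence that could be read as evidence for or against the app, which the design cannot supply.

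**Working it through.** **Design figures.** The plan gives no figure for the subgroups, so its sample size is reproduced only to fix the scale. Inputs from the Sample size section: "Assuming a -2% weight change at 12 months postpartum compared to before pregnancy in the non-intervention group"; the intervention "would result in a -5% weight change at 12 months postpartum"; "standard deviation of 8% and significance level of 5% at 80% power"; "To conduct a two-sided test". The difference is 3 points.
- Normal approximation: n per arm = 2 × (1.960 + 0.842)² × 8² / 3² = 111.6, so 112 per arm and 224 in total.
- t-test version: 112.6, so 113 per arm and 226 in total. This matches "226 participants in both groups are needed".

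**Tracker use as a share of the study period.** Assumption: enrolment 10–30 weeks before delivery. Twelve months is taken as 52 weeks and 24 months as 104.

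| Period counted | Length (weeks) | Compliant control | Intervention woman, daily use to 12 months except the 6-week postpartum pause |
|---|---|---|---|
| To 12 months | 62–82 | 3/82 to 3/62 = 3.7–4.8% | 56/62 to 76/82 = 90–93% |
| To 24 months | 114–134 | 4/134 to 4/114 = 3.0–3.5% | (10+46+1)/114 to (30+46+1)/134 = 50–57% |

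On either count a control who does all that is asked falls far below 60%. Counted to 12 months, the upper stratum holds almost no controls, and the lower stratum sets nearly all controls against intervention women who did not adhere. Counted to 24 months, an intervention woman on her schedule also stays below 60%, so the upper stratum holds only women who wear the tracker beyond what is asked. Neither count leaves a usable comparison.

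**Share of measurements (four subgroups).** The result depends on the denominator.
- Each arm's own schedule: for weighings, 80% is 4 of 5 for a control but hundreds of daily weighings for an intervention woman. The same label selects different women.
- The common schedule only: the denominators match, but membership is still decided after randomisation and can be affected by allocation.

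**Timing.** Of the five common weighings, four come after delivery and one after the 12-month endpoint. Of the four tracker weeks, three come after delivery. In calendar time, 104/134 to 104/114 = 78–91% of the study period follows delivery.

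**Size of the bias: an illustration with no true effect.** Let adherence propensity and weight change be bivariate normal, with correlation r (better adherence, lower weight) and SD 8. If a share p of an arm reaches the cut-off and z is the matching normal quantile, the mean shift is −r × 8 × φ(z)/p in the upper stratum and +r × 8 × φ(z)/(1−p) in the lower. The shares and r are assumptions; the documents give neither.

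Worked case, r = 0.3, with 40% of intervention and 80% of control women reaching the cut-off:
- Upper: −2.4 × 0.386/0.4 = −2.32 and −2.4 × 0.280/0.8 = −0.84; difference −1.48.
- Lower: 2.4 × 0.386/0.6 = 1.55 and 2.4 × 0.280/0.2 = 3.36; difference −1.81.

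Range for r = 0.2–0.5 (intervention minus control; negative favours the intervention):

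| Share reaching cut-off, intervention / control | Upper stratum | Lower stratum |
|---|---|---|
| 40–60% / 80% | −0.5 to −2.5 | −0.7 to −3.0 |
| 80% / 50% | +0.7 to +1.8 | +1.0 to +2.4 |
| 70% / 70%, same selection | 0 | 0 |

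In a simulation with 113 per arm (5,000 runs), with 40–50% of intervention and 80% of control women reaching the cut-off, a nominal 5% t-test rejected in 11–17% of runs at r = 0.3 and in 26–44% at r = 0.5. With equal shares and r = 0.3 it rejected in about 5%.

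**The case against.** The section names no contrast. It says only that subgroup analyses will be done on the endpoints, and one listed endpoint, diet, exists in the intervention arm alone. Adherence is likewise summarised for the intervention arm only. Some of these splits may therefore be meant within one arm. This stands as a real ambiguity. Against it, the secondary-outcome section says so when an analysis concerns the intervention group alone, the subgroup section does not, and the primary and secondary analyses compare groups. A within-arm contrast would not be randomised either.

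Three stronger readings are tempting, and the documents do not support them.

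- A reader might infer that all six subgroups are biased by construction through unequal schedules. That is forced only for the two tracker-use splits read literally. For the other four, the common schedule could be the denominator; bias is then expected but not arithmetically certain.
- A reader might expect a spurious benefit of the app among adherers. That needs a smaller share of intervention women than of controls to reach the cut-off. If the app raises adherence, the shares reverse and so does the sign.
- A reader might take the 1.5-point case as an estimate. It rests on one assumed pair of shares and one assumed correlation.

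It is also fair that the section claims no confirmatory status, and that an article may leave the exact denominator to the full protocol. Defining it would not cure the main fault, because no denominator turns a post-randomisation stratum into a randomised comparison.

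**Conclusion.** The point holds in this form. Six of the nine subgroups condition on adherence after randomisation, and any comparison of arms within them is non-randomised under every denominator.

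For the two tracker-use splits the comparison is unusable as worded. For the four measurement-share splits, bias is expected but its size and sign cannot be fixed from the documents. Under the stated assumptions it spans zero and reaches 2.5 points in the upper stratum and 3.0 in the lower, as large as the 3-point design difference.

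The between-arm reading is inferred from the group comparisons planned elsewhere, not stated outright. The main analysis of the primary outcome does not use these strata and is unaffected.

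**What to change.** - Remove the six adherence-defined splits as between-arm comparisons of the primary and secondary endpoints.
- Report how adherence relates to weight change within the intervention arm only, with a defined denominator and labelled descriptive and non-causal.
- Limit between-arm subgroups to baseline values that allocation cannot have affected, tested by a treatment-by-subgroup interaction. Self-reported pre-pregnancy weight or BMI would qualify. Registration weight, body composition and activity qualify only if confirmed as measured before the intervention starts. The text does not show this: allocation is set before each day's recruitment, the intervention begins on the day of consent, and Table 1 has weight and activity measured at home.

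A complier average causal effect with allocation as instrument is not a ready substitute. App advice and articles can act on weight without device measurement, so the exclusion restriction is doubtful.

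The cost is wording only, with fewer analyses. The one loss is a between-arm table for adherers.

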### Confidentiality

All data will be anonymized using a research ID number. Personal data including name, e-mail, telephone number, and address contained in the consent forms of participants will be stored at each site and by the trial secretariat. The research ID and corresponding table will be stored at each site.

### Monitoring

Although this will be an intervention trial, the intervention is not considered to be invasive. Thus, no data monitoring committee or auditing will be needed. The research coordinator at each site and trial secretariat will regularly discuss the progress of the study and any issues to be addressed. Any modification or inquiry regarding the study will be communicated through the trial secretariat.

### Harms

The intervention planned for this study is not considered to be harmful to the participants. If adverse events occur, the trial secretariat will take appropriate measures in cooperation with the principal investigator at each site.

### Dissemination policy

The study findings will be disseminated at peer reviewed scientific journals and presented at international conferences and conferences in Japan and other countries.

## Discussion

This paper describes the protocol for a randomized controlled trial that aims to determine whether a lifestyle intervention using IoT devices and mobile applications performed during pregnancy to 1 year postpartum will affect weight loss in obese women at 1 year postpartum.

In Japan, the proportion of women of childbearing age with BMI ≥ 25 kg/m^2^ is approximately 10% (National Health and Nutrition Survey, Ministry of Health, Labour, and Welfare). These women tend to have poorer pregnancy outcomes [6, 7]. It has also been reported that in women with gestational diabetes, the risk for developing diabetes mellitus over a mean of 2.2 years postpartum was 3.2 among those who were obese before becoming pregnant compared to non-obese women [23]. However, other long-term data concerning postnatal outcomes are unavailable. In addition, there have been few reports on longitudinal weight changes from before to after pregnancy in obese East Asian women, including Japanese, and no reports on interventions using IoT devices during and after pregnancy in obese Asian women.

The significance of starting the lifestyle intervention during pregnancy in the present study is as follows: (1) lifestyle interventions that start during pregnancy can suppress weight gain during pregnancy, leading to greater postpartum weight loss; (2) as pregnancy is a good opportunity to reexamine one's lifestyle habits, behavioral changes made during pregnancy could lead to lifestyle improvements during the busy postpartum period; and (3) it has been suggested that providing guidance concerning breastfeeding during pregnancy can increase the breastfeeding rate. Once established, a woman could expend 500 kcal per day by breastfeeding, which could help her lose weight. However, obesity is reportedly associated with shorter periods of breastfeeding [24]. In addition, the postpartum period, especially at approximately 6 months postpartum when the baby starts weaning and breast milk decreases, can be a time when weight tends to rebound. Hence, intervening at this time is likely to be important for obese women. Thus, if obese women receive suitable advice at the appropriate time concerning suitable lifestyle habits and breastfeeding is promoted, pregnancy and the first year postpartum period could be a great opportunity for weight correction. However, currently, there are no systems or studies that support this.

In the present study, we will use manga comics as a tool for educating obese pregnant women. Manga comics are commonly employed in Japanese educational culture. In Japan, a wide variety of manga characters appear in textbooks used in compulsory education. Some advantages of manga comics are that (1) use of friendly characters and expressions can increase interest and motivation for learning, (2) use of easy-to-understand illustrations can make it easier to convey content that may be difficult to express in writing, (3) the story can be tailored so the context, background, and content are easy to grasp; (4) placing teachers and students in the manga tends to place the reader in the student's position and help them participate in the process of learning through dialogue with the teacher [25]. To increase awareness of obesity, pregnancy, and childbirth, we created a manga comic that follows a main character (Hana-chan) with a pre-pregnancy BMI of 30 kg/m^2^ from when she becomes pregnant through childbirth and the postpartum period. The comic will be sent to the participants' smartphones.

(Hana-chan application website: https://www.ncchd.go.jp/hospital/about/section/perinatal/bosei/bmi.html).

In the present study, a mobile application will automatically provide individualized advice based on the participant's status during and after pregnancy. This personalized automated advice will consider the weeks of pregnancy or the postpartum period and will be based on the weight, activity, and sleep measurements acquired with the IoT devices and meal photographs and records uploaded to the mobile application. Lifestyle-related interventions such as coaching provided over mobile platforms have been found to have the same effects on weight loss as in-person interventions for obese non-pregnant women [26]. Hence, personalized advice is expected to be effective.

Smartphones and other eHealth technologies are becoming more common in today's society. In Japan, more than 90% of individuals in their 20 s and 30 s use smartphones [27], according to a survey on IT media use and information behavior in 2019 (ICT Policy Institute, Ministry of Internal Affairs and Communications, September 2020). Providing advice through articles and other means delivered via smartphone and receiving automated advice based on IoT device measurements or data recorded with a smartphone application may help promote behavioral changes that will result in sustainable weight loss in obese women. If this can be achieved, interventions consisting of IoT devices and mobile applications could be used in actual clinical practice.

